Randomized controlled trials comparing the combination of tocilizumab and MTX with a switch to tocilizumab monotherapy in rheumatoid arthritis patients with an inadequate response to MTX have reported a higher incidence of liver dysfunction in the combination therapy group [10,11]. Additionally, long-term MTX use is associated with various complications, such as hepatotoxicity, bone marrow suppression, and lymphoproliferative disorders. Given that filgotinib is effective even without MTX, filgotinib monotherapy is expected to offer a safer treatment option while maintaining efficacy in patients with rheumatoid arthritis who do not respond adequately to MTX. Therefore, we aim to compare the efficacy and safety of filgotinib monotherapy with the combination therapy of filgotinib and MTX in patients with moderate to severe active rheumatoid arthritis who had an inadequate response to MTX.

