#### Safety endpoints.

Number of cases and incidence rate of adverse events, clinical laboratory values, and vital signs will be recorded from the first dose until week 48 of study treatment initiation. An adverse event is any undesirable symptom, sign, disease, or abnormal clinical laboratory value that occurs in a subject, regardless of whether there is a causal relationship with the study. Worsening of arthritis is considered an insufficient effect of the study treatment and will not be classified as an adverse event. The principal investigator and others will assess the severity of adverse events in three categories (mild, moderate, and severe). The severity of adverse events (mild, moderate, and severe) will be assessed based on the Common Terminology Criteria for Adverse Events (CTCAE). This assessment of severity is different from the evaluation of the seriousness of the adverse event. A serious adverse event is an adverse event that results in death, is life-threatening, requires hospitalization or prolongation of an existing hospitalization, leads to permanent or significant disability or dysfunction, or causes congenital abnormalities in offspring. On the other hand, hospitalizations without adverse events will not be considered serious adverse events if they fall under the following categories:

1) Hospitalizations for purposes other than the treatment or evaluation of an adverse event (e.g., health checkups).2) Hospitalizations for scheduled surgeries or examinations planned before informed consent, provided there is no change in the patient’s condition after initiating the study treatment.3) Hospitalizations required for the administration of the study drug.4) Hospitalizations for the periodic maintenance of pre-existing medical devices (e.g., battery replacements).

Each investigator will make determinations based on these predefined criteria.

All adverse events must be followed up for 28 days after the completion of study treatment or until recovery, whichever comes first. Additionally, serious adverse events must be followed up until they resolve or, if resolution is not expected, until the symptoms stabilize. However, if it is medically determined that follow-up is not necessary, the follow-up for the adverse event may be discontinued.

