### Study discontinuation criteria

The study will be discontinued if any of the following criteria are met. The principal investigator will promptly inform the principal investigators at each participating medical institution about the decision to discontinue the study. Each principal investigator will promptly notify the subjects and take appropriate medical interventions and other necessary actions.

1) If the number of enrolled subjects is significantly below the target, or if frequent deviations from the study protocol occur, making it difficult to complete the study2) If a serious adverse event is reported and it is determined that there are safety concerns regarding the protocol treatment3) If new information related to the protocol treatment is obtained, such as from publications or conference presentations, and it is determined that there are safety concerns regarding the protocol treatment

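### The serious-adverse-event definition has no category for other medically important events, so some important outpatient events need not be serious and then fall outside SAE follow-up and study-discontinuation criterion 2

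*Protocol article*

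**What the plan says.** All references are to the protocol article.

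- **Definition (Safety endpoints).** "A serious adverse event is an adverse event that results in death, is life-threatening, requires hospitalization or prolongation of an existing hospitalization". The sentence ends with the remaining two routes: "leads to permanent or significant disability or dysfunction, or causes congenital abnormalities in offspring". Four kinds of hospitalization that do not count are then listed, followed by "Each investigator will make determinations based on these predefined criteria".
- **Severity (same section).** Events are graded mild, moderate or severe by CTCAE, and "This assessment of severity is different from the evaluation of the seriousness of the adverse event".
- **Follow-up (same section).** For events in general: "All adverse events must be followed up for 28 days after the completion of study treatment or until recovery, whichever comes first". For serious events: "serious adverse events must be followed up until they resolve or, if resolution is not expected, until the symptoms stabilize". Follow-up may be stopped where it is medically judged unnecessary.
- **Study discontinuation criteria, item 2.** "If a serious adverse event is reported and it is determined that there are safety concerns regarding the protocol treatment".
- **Withdrawal criteria, item 3.** This covers an event that is serious or significant where continuing treatment is judged difficult. Significant is not defined. The same section asks that the clinical course of traceable withdrawn subjects be monitored and reported.
- **Introduction.** "long-term MTX use is associated with various complications, such as hepatotoxicity, bone marrow suppression, and lymphoproliferative disorders". This forms part of the argument for testing filgotinib without methotrexate.

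**The concern.** A definition of seriousness usually ends with a residual category for events that are medically important although they meet none of the concrete outcomes. This one does not. The gap matters because the definition controls two other rules in the article: how long an unresolved event must be followed, and which of the trial's own events can feed the safety-based decision to discontinue the study.

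It also touches the trial's rationale. The Introduction offers less methotrexate toxicity as a reason to study the switch, and the Discussion expects that a positive result could support a strategy with fewer adverse effects. Lymphoproliferative disorder and marrow suppression are harms the authors name. Either may be diagnosed and managed without admission, and may then meet none of the listed criteria. What is at stake is whether such an event is classified consistently and followed to an outcome.

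**Working it through.** No alpha, power, rate or sample size enters this point, and the plan states no figure to reproduce. The check sets the sections side by side.

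**Step 1: is there a residual category?** The definition has five routes: (1) death, (2) threat to life, (3) admission or prolonged admission, (4) permanent or significant disability or dysfunction, (5) congenital abnormality. The last is joined by *or*, and nothing follows it except exemptions from route 3. There is no residual category.

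**Step 2: can severity supply one?** No. Severity and seriousness are explicitly separate assessments ("This assessment of severity is different from the evaluation of the seriousness of the adverse event"), so a severe CTCAE grade does not make an event serious.

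**Step 3: which events are left out?** Only those that miss all five routes. Take a lymphoproliferative disorder, marrow suppression, or a venous thromboembolism (recent history is an exclusion criterion), managed as an outpatient. Route 3 fails by construction, and routes 1 and 5 do not apply. Routes 2 and 4 may or may not apply, depending on the case. Such an event *need not* be serious. It does not follow that it *is not* serious.

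**Step 4: follow-up.**

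| Classification | Required follow-up ends |
|---|---|
| Serious | at resolution or stabilization |
| Not serious | at recovery, or 28 days after study treatment is completed, whichever is first |

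In both rows follow-up can be ended earlier on medical judgement.

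Illustration: the intervention period is 48 weeks. An event first found at week 48 in a subject who completes treatment, and not classified as serious, must be followed to week 48 + 4 = 52 at most, resolved or not. The same event classified as serious has no such cap. A subject who withdraws is treated differently: if traceable, the clinical course is to be monitored and reported whatever the classification. The gap therefore lies mainly with subjects who complete treatment.

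**Step 5: study discontinuation.** Criterion 2 has two conditions: a reported serious event and a determination of safety concerns. An event not classified as serious fails the first, whatever view is taken of the second. Criterion 1 concerns enrolment and deviations. Criterion 3 concerns new information, and its examples are external sources.

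**Step 6: consistency of terms.** Withdrawal criterion 3 recognises a class of significant events alongside serious ones. That class appears neither in the follow-up rule nor in discontinuation criterion 2, and it has no definition.

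**Step 7: detection.** Statistical methods tabulates treatment-emergent events and adverse drug reactions per group by system organ class, preferred term and severity. Central monitoring, about every six months, reviews whether adverse events are present. An event left out in Step 3 still appears there by name and by arm.

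**The case against.** **The list may not be closed.** "Each investigator will make determinations based on these predefined criteria" directly follows the hospitalization exemptions and may refer only to them. The article condenses a full protocol that is not shown, and the trial commits itself to good clinical practice. The ambiguity of that sentence is real, but the point does not rest on it: the definition ends without a residual item. Nor is this silence of the kind an article leaves to its parent document, since the article prints a full definition and four exemptions. If the full protocol does hold the missing category, the article misstates it, and the correction to the article is the same.

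**The effect is limited.** This largely stands. Four stronger readings are tempting, and the documents do not support them:

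- *An outpatient lymphoproliferative disorder or thrombosis is never serious, so seriousness turns on a site's admission habits.* Life-threatening events and significant disability or dysfunction qualify without admission, and dysfunction need not be permanent.
- *Follow-up is lost.* It is capped at 28 days after treatment is completed. Traceable withdrawn subjects are covered separately, and SAE follow-up can itself be waived.
- *The SAE results by arm would be wrong.* The article describes no SAE table, and every treatment-emergent event is tabulated by term and severity.
- *A given share of important safety events would go missing.* The documents give neither a rate for these events nor the fraction managed without admission, so no share can be stated.

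Discontinuation criterion 2 is also not automatic. A determination of safety concerns is needed in any case, so a change in classification opens the route without deciding the outcome.

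**Conclusion.** The point holds in a limited form and is worth correcting. The printed definition lets an important event managed without admission, and meeting none of the five criteria, go unclassified as serious. Two consequences follow from the text: required follow-up of an unresolved event can end 28 days after study treatment is completed, mainly in subjects who complete treatment, and the event cannot act as the serious event in discontinuation criterion 2. The harm is to classification, follow-up duty and that criterion. Detection, the planned safety tables, the primary analysis and the sample size are unaffected.

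No numerical size is given because the documents contain no basis for one. The conclusion assumes that the printed definition is the one sites apply, and that some events of the kinds named are managed without admission and are neither life-threatening nor significantly disabling.

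**What to change.** Add one category to the definition under Safety endpoints: any other medically important event, in the investigator's judgement. Give as examples the harms the protocol itself names, such as lymphoproliferative disorder and bone marrow suppression. A fixed list of conditions that are always serious is not needed and would go beyond the documents.

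Then reconcile three places so that they use the same terms: the definition, the serious-or-significant wording in withdrawal criterion 3 (define significant or align it with the new category), and the serious event required by discontinuation criterion 2. Only the terms need to agree; this point takes no position on when a subject or the study should stop.

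The cost is a sentence in the protocol, a matching field in the EDC system, and a few more SAE reports. The existing rule for following serious events then applies to the added events without rewriting.

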#### Exploratory endpoints.

Change from baseline at week 24 and week 48 in serum amyloid A, serum cytokines, and peripheral blood immunophenotype will be measured. Specifically, serum cytokine levels will be measured using Olink proteomics and/or other methods. Blood lymphocyte subsets, including those defined by the Human Immunology Project, as well as T cell immunoreceptor with Ig and ITIM domains (TIGIT)-positive T follicular helper (Tfh) cells and C-X3-C motif chemokine receptor 1 (CX3CR1)-positive T cells, will be analyzed using flow cytometry and/or other methods [14–16]. Serum cytokine measurements and immunophenotyping will be conducted only at the rheumatology department of Keio University Hospital.

### Data collection

#### Trial visits and examinations.

The study visit schedule and data collection timeline are outlined in Fig 1. The screening period will be within 8 weeks prior to the start of the study treatment. The assessment time points will be counted from the start date of the study treatment (Day 1), with evaluations to be conducted within ±1 week of each time point (weeks 4–12), and within ±2 weeks of each time point (from week 24 onwards).

### Data management, monitoring, and auditing

At enrollment (within 8 weeks prior to the start of study treatment), the following information will be collected and recorded in the EDC system. In addition to this information, the registration number, status of informed consent, and results of the eligibility assessment will also be recorded in the EDC system:

1) Gender2) Age (at the time of consent)3) Race (Asian, American Indian or Alaska Native, Black or African American, Native Hawaiian or Other Pacific Islander, White)4) Height and weight5) Time of rheumatoid arthritis diagnosis6) Treatment history of rheumatoid arthritis (glucocorticoids, DMARDs, NSAIDs, etc.)7) Surgical history related to rheumatoid arthritis8) Medical history and comorbidities9) Smoking history10) 12-lead electrocardiogram (results obtained within 12 weeks prior to consent can be used)11) Infectious disease testing (results obtained within 12 weeks prior to consent can be used; for patients using bDMARDs, pre-treatment results can be used): Either skin tuberculin test or interferon-gamma release assay (IGRA), hepatitis B surface (HBs) antigen, HBs antibody, HB core antibody, and anti- hepatitis C virus antibody. For subjects who are HBs antigen-negative but HBs antibody-positive and/or HBc antibody-positive, HBV-DNA quantification testing must be performed at least once every 6 months as a minimum requirement. This does not preclude more frequent testing, such as every 1–3 months.

The case report forms for this study will be managed using the EDC system, and the registration numbers will be issued through the EDC system. The principal investigator, co-investigators, or research collaborators will promptly enter data into the EDC system after the evaluation/investigation of each participant is completed. In accordance with a separate data management plan, the data center will follow up on delayed data entries, conduct data inquiries, address queries related to the data, make necessary data corrections, manage the database, and prepare datasets for statistical analysis based on the data entered into the database. The principal investigator will ensure that data and records are properly stored for 5 years from the later of the date the study conclusion is reported or 3 years after the final publication of the study results.

Independent monitors will visit the study sites to examine the records, verify them against source documents, and engage with the investigators and site coordinator to observe and discuss the trial’s progress. They are responsible for ensuring compliance with the protocol and guidelines, as well as overseeing the completion of the electronic Case Report Form (eCRF) and other required documentation.

This study is a collaborative research project with Gilead Sciences, Inc., the manufacturer of JYSELECAⓇ (filgotinib). Gilead Sciences, Inc. will be involved in the preparation of the study protocol. However, Gilead Sciences, Inc. will not participate in data collection, data management, statistical analysis, or the evaluation of study results. Therefore, audits are not considered mandatory, and routine audits will not be conducted. The reliability of this study is ensured by the fact that it is not a clinical trial aimed at regulatory approval. Monitoring will be implemented to protect study participants, ensure ethical standards, adhere to clinical research laws and the study protocol, and maintain data reliability and appropriate research practices.

In this study, both central monitoring and on-site monitoring will be conducted. Central monitoring will be performed every six months in principle. It will include the review of progress management items (enrollment progress and status of discontinued cases), safety management items (compliance with the study protocol and the presence or absence of adverse events), and outcome-related items (the implementation status of the primary endpoint, secondary endpoints, and efficacy assessment items). On-site monitoring will be conducted twice: once within three months after the enrollment of the first patient at each site and once after treatment completion or after the enrollment of the last patient at each site. The monitoring will include confirmation of the informed consent process, eligibility of enrolled patients, and compliance with the study protocol with data accuracy.

The accuracy, consistency, and reliability of the data will be scrutinized through independent monitoring, which operates separately from the study investigators as noted above. Furthermore, a steering committee consisting of external experts, independent of the study investigators, will conduct a thorough review of the data.

Furthermore, when publishing papers or presenting at conferences, the conflict of interest (COI) and the role of Gilead Sciences, Inc. in this study will be clearly disclosed. Quality control will be conducted through monitoring, and if significant issues arise or if events with serious implications for participant safety occur, consideration will be given to conducting an ad-hoc audit as necessary.

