### Eligibility criteria

Eligible patients are those who satisfy all the inclusion criteria and do not meet any of the exclusion criteria.

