### Inclusion criteria

1) Patients aged 18 years or older2) Patients diagnosed with rheumatoid arthritis based on the 1987 ACR classification criteria or the 2010 ACR/EULAR classification criteria3) Patients who have received stable treatment with MTX at a dose of at least 6 mg/week or combination therapy with bDMARDs and MTX for at least 8 weeks prior to enrollment but still demonstrate moderate to high disease activity, defined by a DAS28-CRP score of 3.2 or higher4) Patients with at least 2 tender joints and at least 2 swollen joints5) Patients who have not previously used JAK inhibitors6) Patients may receive glucocorticoids at a dose equivalent to 10 mg/day or less of prednisolone7) Patients who have provided written consent to participate in this study

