### Exclusion criteria

1) Patients who plan to become pregnant or give birth between the time of consent and the completion of study treatment2) Patients with an estimated glomerular filtration rate less than or equal to 30 mL/min/1.73 m²3) Patients with aspartate aminotransferase or alanine aminotransferase levels exceeding five times the upper normal limit4) Patients with a white blood cell count below 2000/μL5) Patients with a platelet count below 100,000/μL6) Patients with a history of venous thromboembolism within 2 months prior to obtaining consent7) Patients with a history of acute interstitial pneumonia within 2 months prior to obtaining consent8) Patients with a history of herpes zoster within 2 months prior to obtaining consent9) Patients with a history of hypersensitivity to either filgotinib or MTX components10) Patients who are breastfeeding11) Patients with pleural effusion, ascites, or other similar conditions12) Patients with active tuberculosis13) Patients deemed unsuitable for participation in the study by the principal investigator or sub-investigator

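### HBs antigen is tested at enrolment, but no listed criterion excludes antigen-positive patients and the mandatory HBV-DNA testing does not cover them

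*Protocol article*

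**What the plan says.** Item 11 of the enrolment list in the protocol article (section Data management, monitoring, and auditing) names the infection tests to be done: "Either skin tuberculin test or interferon-gamma release assay (IGRA), hepatitis B surface (HBs) antigen, HBs antibody, HB core antibody", together with hepatitis C antibody. The same item contains the only hepatitis B follow-up rule in the article. It applies to subjects who are "HBs antigen-negative but HBs antibody-positive and/or HBc antibody-positive, HBV-DNA quantification testing must be performed at least once every 6 months". A further sentence permits more frequent testing but does not widen the group to be tested.

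The section Eligibility criteria makes the numbered lists decisive: "Eligible patients are those who satisfy all the inclusion criteria and do not meet any of the exclusion criteria". Those lists contain no hepatitis B criterion. The entries that come closest, all under Exclusion criteria, are:

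- item 3, on liver enzymes: "Patients with aspartate aminotransferase or alanine aminotransferase levels exceeding five times the upper normal limit"
- item 11: "Patients with pleural effusion, ascites, or other similar conditions"
- item 13, the discretionary clause: "Patients deemed unsuitable for participation in the study by the principal investigator or sub-investigator"

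**The concern.** The article itself treats hepatitis B as a risk that calls for viral-load monitoring during study treatment. Yet the limit of its rule takes in subjects with antibody evidence of past infection and leaves out those whose surface antigen shows current infection. Since no criterion turns the second group away at entry, they can be enrolled with less required viral monitoring than the first.

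What is at stake is the safety of an individual participant who newly starts filgotinib. Methotrexate is not a new exposure in either arm, because inclusion item 3 admits "Patients who have received stable treatment with MTX at a dose of at least 6 mg/week", or methotrexate combined with a biologic, for at least 8 weeks before enrolment.

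**Working it through.** The plan gives no figure to reproduce. The check is to follow one patient through the rules as printed, with two simple counts.

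**Step 1: does any criterion use the antigen result?** Inclusion criteria: 7. Exclusion criteria: 13. Total 7 + 13 = 20. Criteria that refer to HBs antigen or to hepatitis B in any form: 0 of 20.

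**Step 2: can an antigen-positive patient pass?** Take a patient who meets all 7 inclusion criteria and is HBs antigen-positive.

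- Exclusion 3 applies only if AST or ALT is above five times the upper limit. At or below that level it does not.
- Exclusion 11 applies only if there is an effusion, ascites or something similar.
- Exclusion 13 applies only if the investigator chooses to use it. It permits refusal but does not require it.
- None of the other exclusions depends on hepatitis B status.

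So the patient is eligible on the printed criteria unless the investigator uses exclusion 13.

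**Step 3: what HBV-DNA testing is then required?** The intervention period is 48 weeks (section The status and timeline of the study). The minimum frequency is once per six months.

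- 48 × 7 = 336 days
- six months = 365.25 / 2 = 182.6 days
- 336 / 182.6 = 1.84 intervals

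| HBV markers at enrolment | Required HBV-DNA tests in 48 weeks |
|---|---|
| Antigen-negative, HBs and/or HBc antibody-positive | at least 1 (2 if the incomplete second interval is covered) |
| Antigen-positive | 0 |

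**Step 4: what else protects the antigen-positive patient?**

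- The antigen result is recorded at enrolment, so the investigator knows it.
- The common laboratory tests (legend of Fig 1) include bilirubin, AST and ALT.
- Withdrawal criteria 3, 4 and 9 allow withdrawal for an adverse event, a worsening comorbidity or investigator judgement.
- Monitoring covers eligibility and protocol compliance. Enrolling this patient without an HBV-DNA test breaches no specific printed rule, so there would be no deviation to find. For the same reason withdrawal criterion 8, which needs a failed eligibility criterion, is not triggered by antigen status.

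These safeguards act on enzymes, clinical events or judgement. None requires viral load to be measured.

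**The case against.** The strongest objection is that this is a journal article. The full protocol is not shown, and the handling of a positive screening test is detail that an article often leaves out. The hepatitis B sentence also sits in a list of data to be recorded. By naming antigen-negative subjects it may presuppose that antigen-positive patients are dealt with elsewhere. It stands that the article nowhere says such patients may be enrolled or need no monitoring, and that the full protocol may cover them. But the article does print numbered lists that it presents as deciding eligibility, and it states the monitoring rule with an explicit limit. Neither the lists nor the rule provides for this group.

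Four stronger readings are tempting and are not supported:

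- **That hepatitis B breaks a pattern set by tuberculosis.** The same item tests for tuberculosis, and exclusion 12 reads "Patients with active tuberculosis". But hepatitis C antibody is also tested and has no matching criterion, so the article does not pair tests with exclusions systematically. The point does not rest on this comparison.
- **That the six-monthly interval is right for antigen-positive subjects.** It was set for antigen-negative subjects, and nothing in the article shows that it suits current infection.
- **That a material number of patients is exposed.** The article gives no prevalence. The number is probably very small, and sites may refuse such patients under exclusion 13.
- **That the trial's result is affected.** Nothing here bears on the sample size, the margin or the primary analysis.

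**Conclusion.** The point holds as a low-frequency participant-safety improvement. On the printed rules an HBs antigen-positive patient with AST and ALT not above five times the upper limit and no ascites or similar condition can be enrolled, at the investigator's discretion, with 0 required HBV-DNA tests. At least 1 is required for a patient with markers of past infection only.

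This rests on two assumptions: that the printed lists are the complete eligibility criteria, as the article presents them, and that no unseen document adds a hepatitis B rule. The second cannot be checked. The counts describe what the text requires; they do not measure clinical risk, and no frequency or bias is claimed.

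**What to change.** Add HBs-antigen positivity to the exclusion criteria. Because the first patient visit was planned for April 2024 and enrolment is ongoing, this reaches only future patients. For any antigen-positive subject already enrolled, require HBV-DNA quantification now, and thereafter at least as often as the article already requires for past infection. The investigators should set the exact interval, which may need to be shorter than six months. If the full protocol already contains such an exclusion, it is enough to correct the published list and apply the testing requirement to anyone enrolled despite it.

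The cost is a protocol amendment, with approval by the Certified Review Board (section Ethical approval), during recruitment at 10 centres, plus very few exclusions or extra blood tests. No new screening test is needed, because HBs antigen is already required at enrolment.
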